##### Caregiver quality of life

We will measure the quality of life of caregivers using the Pediatric Asthma Caregiver’s Quality of Life Questionnaire (PACQLQ) [15]. The PACQLQ has 13 items, each scored on a 7-point Likert scale, with “1” indicating severe impairment and “7” indicating no impairment. The score (range: 1–7) is calculated by taking the average of scores for each item; higher scores indicate better quality of life.

##### Caregiver mental health

We will measure depressive symptoms among caregivers using the Patient Health Questionnaire-9 (PHQ-9). The PHQ-9 has nine items, each scored on a Likert scale of 0–3. Higher scores indicate more evidence of depressive disorder of greater severity of disorder; scores are calculated by summing the scores for all items. We will analyze differences in PHQ-9 score at baseline as compared to 6 months, as well as between treatment groups at 6 months.

##### Medication adherence

We will measure adherence to prescribed asthma medications at baseline and during follow-up visits. First, we will use the Adherence to Refills and Medications Scale-7 [16]. ARMS-7 be will be administered at baseline and monthly during the follow-up period. The score is calculated by summing the scores for all items; lower scores indicate better adherence. Second, we will measure adherence using inhaler counters placed on all daily inhaled medications (e.g. inhaled corticosteroids, long-acting beta agonist, combination therapies). We will evaluate differences in the number of puffs used divided by the number of puffs indicated to have been used by the prescribing physician over the monthly follow-up period.

#### Process evaluation

##### Fidelity to the intervention

We will conduct audio recordings and in-person observations of clinic staff, study staff, and study participants to evaluate fidelity (i.e. how well the intervention was delivered as intended according to the protocol). With participant consent, we will audio record all home visit interactions between nurse managers and families. Using pre-established checklists based on study protocols and standard operating procedures, we will evaluate the extent to which these procedures were followed by nurse managers in a random selection of 20% of audio files.

##### Acceptability and feasibility

We will conduct in-depth interviews and focus group discussions with approximately 30 child–caregiver dyads. These in-depth interviews and focus group discussions will inform understanding of the acceptability and feasibility of the intervention strategy from the perspectives of relevant stakeholders. We will also carry out in-depth interviews with nurse managers and local clinicians. Interviews will be semi-structured; we will have an interview guide but will also probe on relevant themes that emerge during the interview. We will also maintain detailed study records and carry out structured surveys to record information such as the frequency of contact by the participating family with the designated nurse manager, the amount of time spent by the nurse manager carrying out their duties as part of this intervention, and perceived satisfaction on the part of the participating families and nurse managers over time.

### Analytical plan

The primary effectiveness outcome is the mean difference in ACT scores at 6 months of follow-up between intervention and control groups. We will analyze these differences using t-tests; in subsequent analyses, we will use multivariable linear regression methods adjusting for baseline ACT score, and may also adjust for additional factors. The primary analysis will be carried out using an intention-to-treat approach. We will also carry out exploratory subset analyses of the difference in ACT score among individuals with high adherence to preventive therapies. In addition, we will use multivariable linear and logistic regression methods as appropriate to analyze differences in secondary outcomes.

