#### Effectiveness and adoption

##### Asthma control

We will measure asthma control at baseline and monthly using the Childhood Asthma Control Test (cACT) Score (ages 5–11 years) or Asthma Control Test (ACT) Score (ages 12–17 years) [13]. Both questionnaires are scored by summing the scores for all items. Lower scores indicate poorer asthma control; higher scores indicate better asthma control. Scores ≤ 19 for both questionnaires suggest impaired asthma control. The primary outcome will be ACT score at 6 months of follow-up.

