#### Sample size

The primary objective of this pilot trial is to assess the feasibility, acceptability, and preliminary effectiveness of the intervention package in the Peruvian context. With a sample size of 100 participants, assuming a standard deviation of 3.6 and a type II error of 5%, we will be able to detect a difference of 2 in ACT score with 80% power. These calculations were based on preliminary data from a prior epidemiological study of children with asthma in this setting, in which the standard deviation of the ACT score was 3.6 [17]. In order to account for approximately 9% attrition, we arrived at a final sample size of 110 individuals.

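### The primary comparison of 6-month ACT is an unadjusted t-test; the already planned baseline-adjusted model would be at least as powerful and should be primary

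*Protocol article*

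**What the plan says.** The Analytical plan section defines the target: "The primary effectiveness outcome is the mean difference in ACT scores at 6 months of follow-up between intervention and control groups". The next sentence gives the method and the order: "We will analyze these differences using t-tests; in subsequent analyses, we will use multivariable linear regression methods adjusting for baseline ACT score". The t-test is the only method attached to the primary outcome before the text turns to later analyses. The sentence does not call the t-test the primary analysis in so many words, but no other reading fits the order given.

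The Asthma control section shows that the covariate will be available: "We will measure asthma control at baseline and monthly using the Childhood Asthma Control Test (cACT) Score" for younger children, and the ACT for those aged 12 to 17.

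The Sample size section is built on the raw standard deviation from an earlier study, "in which the standard deviation of the ACT score was 3.6", and concludes that "we will be able to detect a difference of 2 in ACT score with 80% power". It makes no allowance for a correlation between baseline and follow-up scores, so it was planned for the unadjusted comparison.

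**The concern.** A child's baseline score on the outcome questionnaire is the natural predictor of the score six months later. A t-test on the 6-month scores leaves the variation that baseline could explain in the error term. The confidence interval is then wider than it need be whenever the two scores are correlated. The unadjusted estimate also carries a share of any chance difference in baseline ACT between the arms, and the Randomization section mentions blocks but no stratification by baseline ACT.

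What is at stake is the precision of the headline result. The trial is sized with no margin at its own 2-point target, so precision given up in the primary analysis is not made good elsewhere in the design.

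**Working it through.** **Inputs.** From the Sample size section: 100 analysed (50 per arm under the 1:1 allocation in the Randomization section), difference 2, SD 3.6, 80% power, about 9% attrition, 110 enrolled. The section also states "assuming a standard deviation of 3.6 and a type II error of 5" per cent. Since 80% power means a type II error of 20%, I take the 5% as the type I error. Sidedness is not stated; I assume two-sided.

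**1. The plan's own figure.** n per arm = 2(1.960 + 0.842)² × 3.6² / 2² = 50.9, so 51 per arm, or 102 against the stated 100. Attrition: 100 / 0.91 = 109.9, so 110. The stated size is therefore reproduced to within two children as an unadjusted, two-sided 5% comparison. Other readings do not fit: one-sided 5% needs 41 per arm, and a literal 5% type II error (95% power) needs 85 per arm.

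**2. Power of the t-test.** Standard error = 3.6 × √(2/50) = 0.72. Noncentrality = 2 / 0.72 = 2.78 on 98 degrees of freedom. Power is 78.5% by noncentral t (79.3% by the normal approximation).

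**3. Power with baseline adjustment.** Residual SD = 3.6 × √(1 − r²), where r is the correlation between baseline and 6-month ACT, with 97 degrees of freedom. The article gives no value for r, so it is an assumption shown as a range.

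| Assumed r | Residual SD | Power | Difference detectable with 80% power | 95% CI half-width (normal) |
|---|---|---|---|---|
| unadjusted | 3.60 | 78.5% | 2.04 | 1.41 |
| 0.1 | 3.58 | 78.9% | 2.03 | 1.40 |
| 0.2 | 3.53 | 80.2% | 2.00 | 1.38 |
| 0.3 | 3.43 | 82.2% | 1.94 | 1.35 |
| 0.5 | 3.12 | 88.8% | 1.76 | 1.22 |
| 0.6 | 2.88 | 93.0% | 1.63 | 1.13 |

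At r = 0.5 the variance falls by r² = 25%. That is worth 100 / 0.75 = 133 analysed children in an unadjusted test. Even at r = 0.1, the degree of freedom spent on the covariate does not bring power below that of the t-test.

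**4. Chance imbalance.** If the baseline SD is also 3.6 (an assumption), the between-arm difference in baseline means has a standard error of 0.72 points. With equal SDs at the two times, the unadjusted estimate shifts by about r times the imbalance. At r = 0.5, a one-standard-error imbalance shifts it by 0.5 × 0.72 = 0.36 points, which is 18% of the 2-point target. Adjustment removes that part.

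**The case against.** The strongest defence is that nothing here is wrong. Under randomization the t-test is unbiased and holds its type I error, and the sample size was calculated for exactly this test. The same sentence of the plan commits to a baseline-adjusted regression, so the adjusted estimate will be produced; the dispute is only over which result comes first. The Sample size section also calls this a pilot concerned with feasibility, acceptability and preliminary effectiveness, where a few points of power matter less than in a confirmatory trial. All of this stands, and it limits the point to efficiency. It does not remove it: the plan still powers a formal comparison, and the better estimator is already planned.

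The defence is also right that the size of the gain is unknown. All children come from one clinic and receive prescribed medication free for six months, so control may change in both arms, and nothing in the article shows that r is high.

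A reader might infer more than the document supports, in three ways:

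- *That the unadjusted test clearly leaves the trial likely to miss a 2-point effect.* This depends on r. From r = 0.1 to 0.3, adjustment adds only about 0.4 to 3.7 percentage points of power; a gain of about 10 points needs r near 0.5.
- *That any baseline imbalance passes in full into the primary estimate.* Only about r times the imbalance does, and the t-test's standard error already allows for such chance variation.
- *That several results, and the clause "and may also adjust for additional factors", leave room to choose the favourable one.* The text puts the t-test first, and the clause applies only to the later model. A closed covariate list is commonly left to a statistical analysis plan, which is not shown here.

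**Conclusion.** The point holds as one of efficiency. The primary analysis of 6-month ACT is a valid but less precise test, while the more precise one is planned as a follow-on using data the trial collects anyway. Power at the planned size is 78.5% unadjusted. With adjustment it is between about 79% (r = 0.1) and 93% (r = 0.6), and the detectable difference falls from 2.04 to between 2.03 and 1.63 points.

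These figures rest on 50 analysed children per arm, the stated SD of 3.6 applying at 6 months, a two-sided 5% test, and an assumed r. The direction of the gain holds at every r in this range; its size cannot be settled from the article. The document does not support calling the planned test invalid, biased or mismatched to the sample size.

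**What to change.** In the Analytical plan section, make the linear model of 6-month ACT on treatment arm with baseline ACT as covariate the primary analysis, and report the adjusted mean difference with its 95% CI as the primary result. Keep the unadjusted t-test as a supportive analysis.

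The cost is a change of wording and one degree of freedom. No new data, visits or participants are needed, and the sample size can stay as it is. The article describes the trial as still enrolling, with data analysts blinded to allocation and no interim analysis planned, so at that stage the change can be made and dated without sight of results by arm.

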### Study outcomes

Trained independent data collectors will administer questionnaires either in person (baseline, 3 months, 6 months) or by phone (months 1, 2, 4, and 5). Details on the frequency and timeline for the following outcomes can be found in Table 2 and a participant timeline can be found in Fig. 3.

**Table 2 Tab2:** Primary and secondary outcomes and frequency of assessment

Domain	Measurement method	Frequency
Asthma control	ACT score ED visits Hospitalizations	Monthly
Preventive healthcare utilization	Number of scheduled clinic visits	Monthly
Disease-specific quality of life	Pediatric Asthma Quality of Life Questionnaire	Baseline, 3 months, 6 months
Caregiver quality of life	Pediatric Caregiver Quality of Life Questionnaire	Baseline, 3 months, 6 months
Caregiver mental health	Patient Health Questionnaire (PHQ) - 9	Baseline, 3 months, 6 months
Medication uptake and adherence	ARMS-7 Inhaler counter Self-reported medication use	Monthly
Intervention engagement	Patient logs Text message transcripts	Throughout
Acceptability	In-depth interviews Focus group discussions Observations	Throughout
Feasibility	In-depth interviews Focus group discussions Observations Time logs	Throughout
Fidelity	Observations Audio recordings Checklists Visit logs	Throughout

*ACT* Asthma Control Test, *ED* Emergency Department

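### The primary test is an unadjusted month-6 t-test that leaves the monthly Asthma Control Test scores unused and is open to bias if loss differs by arm

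*Protocol article*

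**What the plan says.** Under Analytical plan, the protocol article defines the primary endpoint: "The primary effectiveness outcome is the mean difference in ACT scores at 6 months of follow-up between intervention and control groups". The method follows directly: "We will analyze these differences using t-tests; in subsequent analyses, we will use multivariable linear regression methods adjusting for baseline ACT score". The unadjusted t-test is therefore primary and the baseline-adjusted regression comes later. The same paragraph states that "The primary analysis will be carried out using an intention-to-treat approach", without defining the term, and names no longitudinal model for ACT.

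Under Asthma control: "We will measure asthma control at baseline and monthly using the Childhood Asthma Control Test (cACT) Score" or, for older children, the ACT. Study outcomes has the questionnaires given "either in person (baseline, 3 months, 6 months) or by phone (months 1, 2, 4, and 5". Each child can thus have a baseline score and up to five further scores before month 6.

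Under Sample size, power is computed on 100 participants, and then: "In order to account for approximately 9% attrition, we arrived at a final sample size of 110 individuals".

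**The concern.** A two-sample t-test at one time point can use only observed, or imputed, values at that time point. The sample-size section anticipates that about 10 of the 110 randomised children will have no month-6 score. Unless something is done about them, the primary estimate is a comparison of completers. It is then unbiased only if, within each arm, the children lost would have scored like those kept, or if loss and selection are the same in both arms so that the errors cancel.

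Equal loss cannot be taken for granted. Intervention families have a designated nurse manager, monthly home visits, check-ins by telephone or text, and medication brought to them. Control families receive education and obtain their free medication at a health facility. A child lost after month 3 or 4 will already have several ACT scores that show how well controlled the asthma was. The primary test ignores exactly the information that would help to correct for selective loss.

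**Working it through.** **Inputs from the protocol article:** SD 3.6, difference 2, 80% power, 100 analysed, 110 enrolled, about 9% attrition, 1:1 allocation. The 5% error rate is labelled type II in the text. It is read here as a two-sided alpha of 0.05, because that reading reproduces the stated size. **Assumptions not in the documents:** the within-child correlation, and the amount and pattern of loss by arm.

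**1. The plan's own figure.** n per arm = 2(1.96 + 0.842)² × 3.6² / 2² = 50.9, so 51 per arm or 102 in total, against 100 stated. With 50 per arm, 2 / (3.6 × √(2/50)) = 2.78, and Φ(2.78 − 1.96) gives 79.3% power. Then 100 / (1 − 0.09) = 110. The figures reproduce as a month-6 comparison of about 100 children out of 110, so 10/110 = 9.1% are expected to have no score in the test.

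**2. Simple bounds on the bias.** Let the missing children score D points relative to those observed in the same arm (D negative), with fractions f_I and f_C missing in the intervention and control arms. The observed mean exceeds the full-arm mean by −fD, so the bias in the difference (intervention minus control) is (f_C − f_I) × D. With 55 per arm and 10 missing in total:

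| Missing, intervention / control | D = −2 | D = −4 |
|---|---|---|
| 5 / 5 | 0 | 0 |
| 2 / 8 | −0.22 | −0.44 |
| 8 / 2 | +0.22 | +0.44 |
| 0 / 10 | −0.36 | −0.73 |

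For example, (8/55 − 2/55) × (−2) = −0.22. The sign depends on which arm loses more of its poorly controlled children.

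**3. Simulation.** SD 3.6, true month-6 difference 2, equal correlation between visits of 0.3 to 0.7, and dropout that is more likely with a low month-3 ACT, from weak to strong selection:

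| Loss, control / intervention | Average loss | Completer difference | Underestimate |
|---|---|---|---|
| 15% / 2.5% | 8.75% | 1.55 to 1.91 | 22.5% to 4.5% |
| 12% / 6% | 9% | 1.78 to 1.97 | 11% to 1.5% |
| 9% / 9% | 9% | about 2.00 | none |

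The underestimate is (2 − estimate) / 2. At correlation 0.6 and 15% / 2.5%, the completer difference is 1.87, 1.77 and 1.66 for weak, moderate and strong selection. An estimator that predicts the missing month-6 scores from baseline and months 1 to 3 returns 1.99 to 2.02. Prediction from baseline alone recovers only part (1.85 to 1.96), so the later baseline-adjusted regression does not replace the monthly scores.

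**4. Power.** Assume loss is spread evenly after months 1 to 5 and missing at random, with correlation 0.3 to 0.7 and the covariance treated as known. At 9% missing, the effective n per arm at month 6 is 50.8 to 52.9 with a repeated-measures model, against 50.05 for the t-test. Power is 79.9% to 81.5%, against 79.4%. At 20% missing it is 75.5% to 79.3%, against 74.1%. None of this counts the gain from baseline adjustment. If baseline and month-6 ACT correlate at r, adjustment leaves a fraction 1 − r² of the variance: 0.91 at r = 0.3 and 0.51 at r = 0.7.

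**The case against.** A reader might infer that the plan excludes children without a month-6 score. It does not say so. The article gives no missing-data rule, and imputation before the t-test may be set out in the full protocol or analysis plan, which are not shown. That silence is no finding. Inflating enrolment protects power and does not define an analysis set.

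A reader might also infer that the plan contradicts its intention-to-treat label. That depends on a definition the article does not give. The term can mean analysis by assigned arm whatever the adherence, which suits the contrast with the exploratory analysis of highly adherent children. On that reading nothing is contradicted.

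Nor do the documents show that loss will differ. Data collectors follow both arms on the same monthly schedule, both arms get free prescribed medication, and the recruitment section sets out retention measures for everyone. It would be wrong to describe controls as receiving education alone.

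Finally, the larger biases need strong selection. To bring the completer difference down to 1.67 at 15% versus 2.5%, lost controls must score roughly 4.2 to 4.9 points below completers at month 3. With 12% versus 6% and a 2.4-point gap, the completer difference is 1.92. The near-perfect recovery by the alternative estimator follows from generating the loss as missing at random.

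All of this stands and limits the claim. It does not remove the point: the article does fix a single-visit unadjusted test as primary while scheduling the monthly scores that would guard against selective loss.

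**Conclusion.** The point holds in a limited form. The primary method uses month 6 alone. Without imputation it rests on about 100 of 110 children, and in any case it leaves the baseline and month 1 to 5 ACT scores out. Bias arises only if loss related to asthma control differs between arms. It then runs from negligible to about 0.45 points of a target of 2 in the simulated scenarios, and it can go in either direction. With equal loss and the same selection there is essentially none. The rates by arm, the correlation and the selection strength are all assumptions.

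The power gained from partial follow-up is small at the planned attrition, about 0.5 to 2 percentage points, so the case rests on protection against bias, with extra precision from baseline adjustment. Nor would the monthly scores let every randomised child contribute, as a reader might suppose. A child with no post-baseline score adds nothing to the model proposed here, and consent governs whether a withdrawn child's data may be used. The t-test is not invalid. The change is worth making because the data are already scheduled.

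**What to change.** Make the primary analysis a repeated-measures model on ACT at months 1 to 6, with arm, month, arm-by-month and baseline ACT-by-month, and take the month-6 arm contrast as the primary estimate. Include, by randomised arm, every child with at least one post-baseline ACT whose data may be used. Keep the month-6 t-test as a supporting analysis. A sensitivity analysis that shifts the unobserved scores by a fixed amount (delta) is optional.

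The endpoint, visits and sample size stay as they are and no new data are needed. The cost is revised analysis wording, somewhat more programming, and a more complex model that relies on missing at random given the earlier scores. The month terms absorb a difference between telephone and in-person scores only if it is similar in both arms, and the plan should say so. The article states that data analysts are blinded to assignment, so the change can be made before anyone analysing the data sees results by arm.

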#### Sample size

The primary objective of this pilot trial is to assess the feasibility, acceptability, and preliminary effectiveness of the intervention package in the Peruvian context. With a sample size of 100 participants, assuming a standard deviation of 3.6 and a type II error of 5%, we will be able to detect a difference of 2 in ACT score with 80% power. These calculations were based on preliminary data from a prior epidemiological study of children with asthma in this setting, in which the standard deviation of the ACT score was 3.6 [17]. In order to account for approximately 9% attrition, we arrived at a final sample size of 110 individuals.

### Data management and quality assurance

Questionnaire-based data will be collected using the Research Electronic Data Capture software (REDCap, Vanderbilt University Medical Center, Nashville, TN, USA). Data will be reviewed for accuracy and completeness on a weekly basis by two parties (data management team, study Principal Investigator [PI]).

To protect confidentiality, all participants will be assigned a unique identification code, which will allow data to be de-identified and stored without identifying information. Transcriptions and research notes will contain no identifying information. Pseudonyms for participants and locations will be used in all transcripts and research notes. Only members of the study team, including the PI and staff researchers, will have access to this data. Due to the low risks associated with this behavioral intervention, there are no pre-specified interim analyses or stopping rules.

